## Trial design {8}

This study is a stepped wedge randomised controlled study, conducted in 10 wards of one acute Australian hospital over 36 weeks. A stepped wedge design allows all wards to receive the intervention at different times, with each ward acting as its own control. Each cluster will comprise two wards. One cluster will switch to the intervention every 6 weeks. This study design reduces the influences of confounders such as variations in size and case mix and supports feasibility while maintaining rigour. This design also allows research staff to work with individual wards as they adopt the intervention, maximising consistency of intervention and aiding implementation (Fig. 1).

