#### Audit and feedback

The benefits and role of audit, including the use of fluorescent markers (FM), in assessing environmental cleaning, is well documented (7,13,14). Audit and feedback to the cleaning staff involved in the additional cleaning will include the use of FM technology, in which invisible gel dots that are removed by cleaning are applied to surfaces. The dots are invisible to the naked eye, resist dry abrasion, and are removed completely by routine cleaning. A structured auditing approach, with staff feedback underpinned by education, will aid improvements in cleaning, as shown in multiple studies (7,13,14). FM auditing of shared equipment will be conducted fortnightly in each ward.

During the intervention phase, audit results will be reported verbally to the cleaning staff, with a follow-up email to cleaning supervisors and the Nursing Unit Managers. Audit results will be used to inform further informal face-to-face education and training. In discussing audit results, informal goals for the next audit will be set with the cleaners. Additional reports will be provided for internal committees, such as the Infection Prevention and Control committee at the conclusion of the study.

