### Outcomes {12}

The primary outcome is the proportion of inpatients aged ≥ 18 years old with a HAI as measured by a HAI point prevalence study (PPS). The secondary outcomes are the thoroughness of cleaning as being the proportion of dots that were completely removed, as measured by the FM gel and ultraviolet light system, and the cost-effectiveness of the intervention compared with routine cleaning.

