#### Secondary outcome analysis

##### FM
audits

We will analyse data from fortnightly cleaning audits using a binomial generalised linear mixed model with a logit link function on the proportion of equipment that were deemed ‘cleaned’. A random intercept will be included for each ward. The effect of the intervention will be tested in three ways: a binary intervention effect, to model an immediate improvement in cleaning; a linear intervention effect, defined as weeks after each ward’s intervention start date, to model a more gradual improvement over time; and a combined binary–linear intervention effect. As per the analysis of the primary outcome, the intervention effect will switch from ‘no’ to ‘yes’ 1 week after the start of the intervention period.

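### The fluorescent-marker audit model names no calendar-time term, so a hospital-wide trend in cleaning would bias its intervention effect, up or down; its outcome unit also needs reconciling.

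*Protocol article*

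**What the plan says.** The Trial design section describes a study "conducted in 10 wards of one acute Australian hospital over 36 weeks", in which "One cluster will switch to the intervention every 6 weeks". Under Audit and feedback, "FM auditing of shared equipment will be conducted fortnightly in each ward".

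The FM audits paragraph of the secondary outcome analysis specifies a binomial mixed model with a logit link. Its terms are a ward effect and an intervention effect in three alternative forms: "A random intercept will be included for each ward. The effect of the intervention will be tested in three ways: a binary intervention effect", then a linear form, then both together. The linear form is "a linear intervention effect, defined as weeks after each ward’s intervention start date".

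One feature is carried over explicitly from the primary analysis: the intervention indicator switches one week after the start. Study time is not mentioned.

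The Primary outcome analysis section does include study time, as a categorical fixed effect with a linear version also tested. It gives control of unrelated change over time as the reason for the linear term.

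On the outcome, the Outcomes section declares "thoroughness of cleaning as being the proportion of dots that were completely removed". The FM audits paragraph instead puts the model "on the proportion of equipment that were deemed" clean.

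**The concern.** In a stepped wedge, time and intervention are confounded by design: each ward has its control data first and its intervention data later. A ward intercept removes stable differences between wards but not change over time. If nothing else in the model carries calendar time, a trend common to all wards is partly read as an intervention effect. The linear form does not solve this, because it counts weeks since the ward's own start and so cannot describe change during control periods.

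The Additional cleaning section makes the FM audit the measure of intervention fidelity. Readers will use it to interpret the infection result, above all if that result is null. A false cleaning gain would suggest that the intervention was delivered and did not work. A masked gain would suggest that it was not delivered.

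The outcome mismatch is a separate, smaller matter. The binomial numerator and denominator are not fixed until the article says whether the unit is a dot or an item of equipment.

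**Working it through.** **No FM figure to reproduce.** The article gives no sample size or expected effect for the FM audits. Its one sample-size figure, for infections, is 132 per cluster-period (132 × 5 × 6 = 3960). The Hussey-Hughes stepped-wedge variance with categorical period effects, 11% versus 0.65 × 11% = 7.15%, and a correlation of 0.3 gives 131, with 80.4% power at 132. The formula that reproduces the plan's own figure thus contains the time terms that the FM model does not name.

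**Inputs from the article.** 36 weeks; five two-ward clusters crossing at weeks s = 6, 12, 18, 24 and 30; fortnightly audits, so 18 per ward.

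**Gap within a ward.** Mean control time is s/2 and mean intervention time is (s + 36)/2. The difference is 36/2 = 18 weeks for every s. Moving the switch by one week does not change this.

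**Gap with wards fully pooled.**

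- Control: Σ(s²/2)/Σs = (1980/2)/90 = 11 weeks.
- Intervention: Σ[(36² − s²)/2]/Σ(36 − s) = (4500/2)/90 = 25 weeks.
- Gap: 25 − 11 = 14 weeks.

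**The planned random intercept lies between.** Let p be the share of a ward's audits under intervention: 5/6, 4/6, 3/6, 2/6, 1/6.

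- The average within-ward variance of the indicator is 7/36 and the between-ward variance is 2/36.
- All wards have the same mean calendar time, so between-ward information carries no linear drift.
- In a linear approximation the absorbed time is 18 × 7/(7 + 2λ) weeks, where λ = 1/(1 + nσ_u²/σ_e²) runs from 0 (fixed ward effects, 18 weeks) to 1 (full pooling, 14 weeks).
- Illustration with assumed values: ward SD 0.3 on the logit scale, 35% cleaned (σ_e² = 1/(0.35 × 0.65) = 4.40), 10 or 20 items per audit (n = 180 or 360 per ward). Then λ = 0.21 or 0.12, and about 17 weeks of drift are absorbed.

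**In percentage points.** 14 to 18 weeks is 2.33 to 3 six-week periods. An assumed drift of 1 point per period gives 2.3 to 3 points; 3 points per period gives 7 to 9. Overall, roughly 2 to 9 points.

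**Simulation with no true intervention effect.** 10 wards × 18 audits, linear drift on the logit scale, 10 or 20 items per ward-audit, ward SD 0.3, 200 runs per setting. Fixed ward intercepts stood in for the random intercept, so these results sit at the 18-week end. The binary form without time gave:

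| Assumed proportion cleaned, week 0 to 36 | Estimated odds ratio | Rejected at nominal 5% |
|---|---|---|
| 30% to 30% | 1.00 | 4% |
| 30% to 35% | 1.11 to 1.14 | 15% to 32% |
| 30% to 40% | 1.24 to 1.26 | 47% to 79% |
| 30% to 50% | 1.52 to 1.54 | 95% to 100% |
| 50% to 40% | 0.81 to 0.83 | 47% to 72% |

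The 30% to 40% row is 10/6 = 1.7 points per six weeks, inside the assumed range. Its full-drift odds ratio is 1.56, and √1.56 = 1.25, as expected when half the drift is absorbed. Under drift, the weeks-since-start form without time also rejected in 21% to 100% of runs. With linear or categorical calendar time added to the binary form, the odds ratio under drift was 0.98 to 1.02 and rejection 4.5% to 8.5%. Simulation error is at most about 3.5 percentage points (one standard error).

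**The case against.** The strongest reply is that silence is not exclusion. The primary analysis text sits under a heading that covers primary and secondary outcomes, and one of its sentences says in general terms what models will contain, including a time effect. This is a condensed article, and a fuller analysis plan may list every covariate. That reading is possible but not the natural one. The sentence stands under the primary-outcome subheading, and the FM paragraph restates the ward intercept, adds its own intervention terms and takes over only the one-week switch. Followed as written, it gives a model without calendar time.

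The reply also notes that the article limits drift: the dots are invisible, control wards do not receive audit results, FM auditors are blinded, wards and cleaning staff learn their allocation two weeks ahead, and the hospital undertakes to avoid significant changes in cleaning policy. These points stand, and they are why the drift size must remain an assumption. They do not rule out a trend, and the Discussion itself lists changes in policy or practice as a limitation. If trained staff carried new habits into control wards, that would be contamination, which a time term does not simply remove.

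Some stronger readings are tempting but not supported:

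- That weeks since start is calendar time under another name. It has a different origin in each sequence and cannot follow change before the switch, so the two are correlated but distinct.
- That three effect forms invite reporting the best one. All three are prespecified, binary and linear each with a reason, and naming a lead form for a secondary outcome is ordinary analysis-plan content.
- That the modelled outcome necessarily differs from the declared one. If each item carries one dot, the two coincide; the article does not say.

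**Conclusion.** The concern holds for the FM audit analysis. As written, its intervention effect is open to bias from secular trend, in the direction of that trend. The binary effect would absorb about 14 to 18 weeks' worth of a linear drift, or roughly 2 to 9 percentage points for an assumed 1 to 3 points per six weeks. Eighteen weeks is exact only for within-ward estimation of a linear trend; the planned random intercept gives somewhat less.

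A reader might infer that any drift inflates the FM result. It does not: a decline would hide a real gain, and a rise followed by a fall could partly cancel. A reader might also infer that the infection result is compromised. It is not, because that model adjusts for study time. A large true cleaning effect could also exceed the bias.

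The size rests on assumptions that the article does not supply: the drift, the proportion cleaned, the items per audit and the ward variance. The direction and the 14-to-18-week range for linear drift follow from the design alone. The dots-versus-equipment discrepancy is real in the text, but matters numerically only if items carry more than one dot.

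**What to change.** State that study time enters all three FM models alongside the intervention terms, in the way set out for the primary outcome: categorical, with a linear version also tested. Linear and categorical time both removed the bias in the simulations.

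Use one FM outcome throughout. Either model dots completely removed out of dots assessed, as the Outcomes section declares, or state how dots map to an item of equipment counted as clean.

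The cost is a change of wording and a wider interval for the FM effect. No extra data are needed, since audits already run fortnightly in every ward.

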##### Cost-effectiveness

The costs of adopting the intervention will be prospectively collected from hospital records, such as the cost of cleaning consumables. Excess length-of-stay estimates will be sourced from studies identified by systematic reviews to estimate the value of bed days saved. The cost-effectiveness of the intervention will be evaluated from the perspective of the hospital decision-maker. Cost-effectiveness will be summarised by the incremental cost-effectiveness ratio and net monetary benefit, which offer different summaries of the change in costs versus health benefits. Modelled changes in the primary outcome (HAIs) will be used to estimate changes in health benefits from cases prevented by the intervention, as quality-adjusted life year (QALY). Probabilistic sensitivity analysis will be undertaken to account for uncertainty in model parameters and its impact on cost-effectiveness outcomes.

Uncertainties in parameter estimates will be captured using appropriate statistical distributions to describe the variability. The fitted distributions will be subject to random re-samples simulated 10,000 times. The distributions of all prior parameters are used to estimate the posterior distributions of ‘change to costs’ and ‘change to QALY’ outcomes. The decision will be informed by plotting cost-effectiveness acceptability curves with threshold values between zero and 100,000 per QALY gained and using the net monetary benefits framework. These approaches are semi-Bayesian and appropriately account for all parameter uncertainty for the adoption decisions.

### Interim analyses {21b}

There will be no interim analysis as we do not expect there to be any negative effects from this study.

### Methods for additional analyses (e.g. subgroup analyses) {20b}

Not applicable—there are no subgroup analyses planned.

### Methods in analysis to handle protocol non-adherence and any statistical methods to handle missing data {20c}

Statistical analyses will be performed as intention-to-treat, in accordance with the published protocol. For the specified study design, the intention-to-treat analysis will assume cluster transitions from control to intervention according to randomised sequence allocation and include all patients who meet the study inclusion criteria.

Missing data will be handled by complete case analysis. Given the use of standardised data collection instruments and protocols, missing data on primary and secondary outcomes is expected to be low. Any deviations from the protocol will be documented and reported in planned research outputs.

### Plans to give access to the full protocol, participant-level data and statistical code {31c}

Fully de-identified data sets and statistical codes will only be available by contacting a chief investigator and providing the appropriate ethical approvals.

## Oversight and monitoring

### Composition of the coordinating centre and trial steering committee {5d}

The project consists of a management and steering committee. The management committee (coordinating centre) will oversee the day-to-day running of the trial and decide on the operational elements of the trial. Members of the coordinating centre are two chief investigators and the trial coordinator. The steering committee will meet as required to provide oversight of the study. The steering committee will have accountability and responsibility for the project, including progress towards completion of agreed project activities (milestones/ deliverables), risks arising and how these are being managed to ensure project outcomes, and research reports. The steering committee consists of all chief investigators and the trial coordinator. Associate investigators are non-voting members of the Steering Committee.

### Composition of the data monitoring committee, its role and reporting structure {21a}

The study does not have a data monitoring committee. The intervention is an enhancement of existing health services delivery (cleaning) with no anticipated risks. There is no planned interim analysis.

### Adverse event reporting and harms {22}

The trial coordinator is responsible for ensuring that all adverse events observed by the investigator/s, study team or reported by sites are collected and recorded in the source documents. The trial coordinator will notify the approving ethics committee of serious adverse events occurring at any of the sites. Adverse events could require reporting as per hospital-specific policy.

### Frequency and plans for auditing trial conduct {23}

The HREC granting approval for this study may conduct an external audit at any point in the trial. The steering committee will be responsible for monitoring risks and the progress of the trial.

### Plans for communicating important protocol amendments to relevant parties (e.g. trial participants, ethical committees) {25}

Where there are any ethical amendments to the trial protocol, approval will be sought from the approving HREC. Similarly, important protocol modification will be updated on the Australian and New Zealand Clinical Trial registry.

## Dissemination plans {31a}

The investigators will implement a dissemination plan that will include key communication strategies for all stakeholders, an open-access publication plan, authorship requirements and publication standards that align with NHMRC Australian Code for the Responsible Conduct of Research (http://www.nhmrc.gov.au/guidelines-publications/r39) and an International Committee of Medical Journal Editors Recommendations for the Conduct, Reporting, Editing, and Publication of Scholarly Work in Medical Journals (http://www.icmje.org/recommendations/browse/roles-and-responsibilities/defining-the-role-of-authors-and-contributors.html).

## Discussion

The CLEEN study is a large cluster randomised controlled trial conducted in an Australian tertiary hospital. The study represents the first randomised controlled study in the world to provide level 1 evidence on the impact of additional cleaning of shared equipment on rates of HAIs (5). The advantages of the study design include a simple and feasible intervention, with strategies built in to ensure adherence and fidelity. Unlike pragmatic trial designs, which may use existing resources of PSAs, we are able to ensure that the intervention is delivered through additional resources being provided specifically for the purpose of delivering the intervention. The stepped wedge design is another strength of the research design, as each ward will act as its own control. This negates issues associated with differing patient case mix, individual ward culture, operational issues and local practices. This study will provide evidence to inform the development of a future service delivery model, national guidelines and local policy with respect to roles and responsibilities and the importance of cleaning of shared medical equipment.

Limitations to the study may include issues such as hospital changes in policy or practice that may influence the outcomes being observed. However, the hospital is committed to ensuring that there will be no significant changes to the hospital cleaning policy during the trial period unless absolutely necessary. Other aspects of infection prevention control policy such as hand hygiene and antimicrobial usage will be monitored, and we will be able to document/identify changes in other policies that may influence the outcomes of this study. Further potential disadvantages of the trial may include that the intervention will only be delivered 5 days of 7, due to physical and financial constraints. Given the intervention is being delivered over the vast majority of the working week, the burden and risk in the environment will still likely be significantly reduced. Environmental swabbing of the environment was considered; however, due to poor positive predictive value, it was not included in the current study design (17). In a related study in the same participating hospital, we intend to use targeted whole genome sequencing to evaluate potential transmission pathways through shared medical equipment.

## Trial status

The trial protocol V1.1. is the current and approved version as of 21 September 2022. Hospital recruitment is completed, including all required ethical approvals. Data collection will begin in March 2023 with an expected end date for data collection in November 2023.

## Data Availability

Details about the study will be posted on information boards in the participating hospital. Standard operating procedures for cleaning specific items of shared medical equipment will be developed and subsequently explained at the in-service (if they are not already in existence at the hospital). These will also be readily available for staff for future reference as needed. Availability of data may be available upon reasonable request, by contacting a chief investigator and providing the appropriate ethical approvals.

## Abbreviations

HAI: Healthcare-associated infection
CLEEN: CLEaning and Enhanced disiNfection
NHMRC: National Health and Medical Research Council
RCT: Randomised control trial
REACH: Researching Effective Approaches to Cleaning in Hospitals
TGA: Therapeutic Goods Administration
FM: Fluorescent markers
HREC: Human Research Ethics Committee
PPS: Point prevalence survey
QALY: Quality-adjusted life year
